## Abstract

**Background:**

Multifocal atrophic gastritis and intestinal metaplasia are considered to be important links in the gastric precancerous cascade. However, there are no specific drugs for these conditions. Although many studies have shown that traditional Chinese medicine is effective with no serious side effects, these studies have not been scientifically rigorous trials. Our aim is to design a high-quality trial for a Chinese patent medicine, Elian Granules, to investigate its efficacy and safety in treating patients with chronic atrophic gastritis with or without intestinal metaplasia.

**Methods:**

This is a phase II, randomized, double-blind, placebo-controlled, multicenter clinical trial. A total of 240 participants will be assigned to a treatment or placebo control group in a 1:1 ratio. The experimental drug or placebo will be taken with boiling water, two small bags (24.2 g) each time, twice a day, half an hour after a meal, for 24 weeks. The primary outcome is the observation of histological changes in the gastric mucosa of patients with atrophic gastritis with or without intestinal metaplasia after 6 months based on the OLGA/OLGIM staging systems. The secondary outcomes include the assessment of dyspepsia and quality of life based on the dyspepsia symptom score and the quality-of-life scale.

**Discussion:**

This study is designed to evaluate the efficacy and safety of Elian Granules in a randomized, double-blind, placebo-controlled, multicenter manner. This trial may not only provide evidence for a phase III clinical trial, but also an alternative option for the treatment of chronic atrophic gastritis (CAG).

**Trial registration:**

Registry Platform For Evidence-Based Traditional Chinese Medicine ChiMCTR2000003929. Registered on 13 September 2020

## Administrative information

Note: the numbers in curly brackets in this protocol refer to SPIRIT checklist item numbers. The order of the items has been modified to group similar items (see http://www.equator-network.org/reporting-guidelines/spirit-2013-statement-defining-standard-protocol-items-for-clinical-trials/).

## Introduction

### Background and rationale {6a}

Despite the declining incidence of gastric cancer, it remains one of the most common and lethal malignant tumors worldwide, especially in Asian countries [1]. This is closely related to the high prevalence of *Helicobacter pylori* (*H. pylori*) infection in Asia [2]. The association between intestinal metaplasia, non-cardiac gastric cancer, and *H. pylori* infection has been confirmed [3]. The pathogenesis is defined by the gastric precancerous cascade [4]: normal gastric mucosa →→ superficial gastritis (later renamed non-atrophic gastritis, NAG) →→ multifocal atrophic gastritis (MAG) without intestinal metaplasia →→ intestinal metaplasia of the complete (small intestinal) type →→ intestinal metaplasia of the incomplete (colonic) type →→ low-grade dysplasia (low-grade noninvasive neoplasia) →→ high-grade dysplasia (high-grade noninvasive neoplasia) →→ invasive adenocarcinoma. Studies have shown that the eradication of *H. pylori* can reduce the incidence of gastric cancer from 63 per 100,000 person-years to 14.8 per 100,000 person-years in the commonly infected population, which is close to the incidence of 1127 per 100,000 person-years in the non-infected population. However, in the severe atrophic gastritis population, the incidence of gastric cancer in the uninfected and *H. pylori*-eradicated patients is still 75.9 per 100,000 person-years and 1.163 per 100,000 person-years, respectively [5]. In patients with intestinal metaplasia or dysplasia, eradication of *H. pylori* does not reduce the risk of gastric cancer [6, 7]. Therefore, Correa et al. believe that multifocal atrophic gastritis is the first true step in the gastric precancerous cascade [4]. However, there is a lack of specifically recognized drugs for the treatment of atrophic gastritis and intestinal metaplasia. COX inhibitors, nonsteroidal anti-inflammatory drugs (NSAIDs), Rebamipite, moluodan, and antioxidant vitamins have been suggested to be potentially effective against atrophic gastritis and intestinal metaplasia, but the quality of evidence is low. Currently, the eradication of *H. pylori* and endoscopic monitoring are the only accepted cost-effective coping strategies [6, 7].

With the widespread use of gastroscopy and pepsinogen treatment, increasing numbers of studies have shown that Chinese herbal medicine and Chinese patent medicine may be effective for atrophic gastritis and intestinal metaplasia; unfortunately, the overall research quality is low. Elian Granules is a Chinese patent medicine used in our hospital which has been in clinical use for over 20 years. It is composed of zedoary turmeric, coptis, codonopsis, salvia, angelica, dandelion, *Oldenlandia diffusa*, rhizoma atractylodis, raw licorice, pinellia, tangerine peel, and tuckahoe and has the effects of clearing heat, promoting blood circulation, and invigorating the spleen. Our preliminary studies have shown that Elian Granules can not only improve the clinical symptoms of patients with atrophic gastritis with or without intestinal metaplasia, but also may reduce gastric mucosal atrophy or intestinal metaplasia in some patients [8, 9]. The results of animal experiments have shown that Elian Granules can reverse the heterogeneity of gastric mucosal epithelial cells and reduce polyploidy and the DNA content in model rats. This reversal may be achieved by promoting the protein expression of the Fas gene and inhibiting that of Bcl-2, leading to the induction of apoptosis in gastric mucosal epithelial cells and an increased ratio of superoxide dismutase to malondialdehyde [10–12].

### Objectives {7}

The purpose of this study is to evaluate the efficacy and safety of Elian Granules in the treatment of chronic atrophic gastritis. The efficacy endpoint of the study is carcinogenesis. The safety endpoint will be determined by the number of (treatment-related) adverse events.

### Trial design {8}

The study is a randomized, double-blind, placebo-controlled, multicenter clinical superiority trial. The patient allocation ratio is 1:1. Figure 1 shows the flow chart of this trial.

**Fig. 1 Fig1:**
[figure not shown]
Study flow chart

## Methods: participants, interventions, and outcomes

### Study setting {9}

Two hundred forty patients will be enrolled from 10 hospitals in 6 provinces in China, including (1) Shuguang Hospital affiliated with Shanghai University of Traditional Chinese Medicine; (2) Yueyang Hospital of integrated traditional Chinese and Western Medicine, Shanghai University of Traditional Chinese Medicine; (3) Shanghai Pudong Guangming Hospital of Traditional Chinese Medicine; (4) The First Affiliated Hospital of Guangxi University of Chinese Medicine; (5) Affiliated Hospital of Changchun University of Traditional Chinese Medicine; (6) Affiliated Hospital of Shanxi University of Traditional Chinese Medicine; (7) The Second Hospital of Anhui Medical University; (8) The Second Affiliated Hospital of Anhui University of Traditional Chinese Medicine; (9) Traditional Chinese Hospital of Lu’an; and (10) Hangzhou Hospital of Traditional Chinese Medicine, and are considered for inclusion if they meet the criteria as defined below, as shown in Fig. 2.

**Fig. 2 Fig2:**
[figure not shown]
Hospital location

### Eligibility criteria {10}

#### Diagnosis

Diagnosis will be made in accordance with the Chinese Consensus on Chronic Gastritis (2017, Shanghai) formulated by the Society of Digestive Diseases, Chinese Medical Association [13]. The diagnostic criteria for chronic atrophic gastritis are as follows.

#### Clinical manifestations and physical signs

Chronic gastritis has no specific clinical manifestations, such as epigastric pain, distention, belching, acid regurgitation, nausea, vomiting, and loss of appetite. The presence or absence of dyspepsia and its severity do not correlate significantly with the classification of chronic gastritis, its endoscopic features, or gastric mucosal histopathologic staging. Most patients have no obvious physical signs, although sometimes mild upper abdominal tenderness or discomfort may occur.

#### Endoscopic and histopathological diagnosis

The endoscopic findings of chronic atrophic gastritis include mixed red and white coloration of the mucosa dominated by white mucosa, flat or even absent folding, exposure of part of the mucosal blood vessels, and a possible association with mucosal granules or nodules. The diagnosis of chronic atrophic gastritis includes both endoscopic and pathologic diagnoses, while atrophy diagnosed under white-light endoscopy has a low concordance with a pathologic diagnosis. The final diagnosis should be based on the pathologic diagnosis. The endoscopic gastric pattern is defined according to the Kimura-Takemoto classification (Table 1), based on the location of the endoscopic atrophic border (Fig. 3). The histopathological diagnosis refers to the pathological diagnostic criteria of chronic gastritis in China and the visual analog scale [13]. The severity of atrophic gastritis is defined according to OLGA and OLGIM [14, 15].

**Table 1 Tab1:** Kimura-Takemoto classification

Type	Classification	Definition
Closed Type	C-1	Atrophy visible in the antrum but not in the corpus
	C-2	Atrophy visible parabolically above the angulus and below the middle of the stomach on the lesser curvature
	C-3	Atrophy visible parabolically above the middle of the stomach on the lesser curvature
Opened Type	O-1	The atrophic border lies between the lesser curvature and the anterior wall
	O-2	The atrophic border lies on the anterior wall
	O-3	The atrophic border lies between the anterior wall and the greater curvature

**Fig. 3 Fig3:**
[figure not shown]
Extension of the atrophic border and patterns of endoscopic gastric atrophy as classified by Kimura and Takemoto

#### Inclusion criteria

Patients must meet the following criteria to be eligible for enrollment:Patients aged 18–70 years, male or femalePatients who meet the diagnostic criteria of chronic atrophic gastritis and who test negative for *Helicobacter pylori* (13C or 14C urea breath test is required)Patients with a pathological stage of OLGA-II/III. Two experts from the Department of Pathology will perform the diagnosis (pathological film reading), with consensus on the pathological conclusionPatients who have voluntarily agreed to participate and who have signed informed consent

#### Exclusion criteria

If the patients meet any of the following criteria at the screening visit, they will not be eligible for the study:Patients with peptic ulcer, severe dysplasia of the gastric mucosa, or suspected pathological diagnosis of malignant transformationPatients with severe diseases of the digestive system or a history of abdominal surgeryPregnant or lactating womenPatients with severe heart and lung diseases, malignant tumors, severe diabetes mellitus, and chronic liver and kidney dysfunction and those in whom the ALT and AST levels indicative of deteriorated liver function are more than 1.5 times the upper limit of normal and in whom there is renal function damage (BUN > 1.2 times of the upper limit of normal; Cr > the upper limit of normal)Patients in whom the PLT is < 1.5 times that of the lower limit of normalDisabled patients (blind, deaf, dumb, mental disorder, physical disability) as prescribed by lawAlcoholicsThose who are known to be allergic to two or more types of drugs or the ingredients of the drug and have allergic constitutionsPatients who have participated in other clinical trials during the previous 4 weeks. Patients who have taken Weifuchun, Moluodan, and folic acid within the previous 2 weeksPatients who, in the opinion of the investigator, are likely to be lost to follow-up or are not suitable for inclusionPatients who withdraw their informed consent

### Who will take informed consent? {26a}

Patients with chronic atrophic gastritis confirmed by histopathology will be screened for eligibility to participate in this study based on the abovementioned criteria. After the patient has been assessed as eligible, he/she will receive the initial study information. After at least 2 weeks of reflection, patients are invited to meet with the research physician to discuss any remaining questions and sign the informed consent.

### Additional consent provisions for the collection and use of participant data and biological specimens {26b}

No additional consent provisions.

## Interventions

### Explanation for the choice of comparators {6b}

Because there is no specific drug for the treatment of chronic atrophic gastritis with or without intestinal metaplasia, it is ethical to conduct this study as placebo controlledA 6-month course of treatment is appropriate and will not delay the patient’s conditionA statistically significant minimum number of cases will be used in this studyPatients will be informed about the content of the placebo treatment and will sign informed consentThe safety of the placebo will be ensured by endoscopic review after treatmentIn order to protect patients, the protocol provides that the investigator may withdraw the patients if the patient’s condition changes during the trial and other effective treatments are neededIt is helpful to objectively evaluate the safety and effectiveness of Elian Granules with controlled evaluations

### Intervention description {11a}

Elian Granules and placebo are produced by the Jiangyin Tianjiang Pharmaceutical Co. Ltd., China, for clinical research only (Approval No. 2006338). The placebo consists of 36% maltodextrin, 11% lemon yellow intermediate, 15% sunset yellow intermediate, 18% caramel intermediate, 4% bittering agent, 1% traditional Chinese medicine essence, and 10% lactose.

Although the placebo is similar to Elian Granules in color and smell, it is not the same. To make a blind test possible, all the drugs will be concealed in uniform, sealed, and opaque packages with the same labels that contain the drug name, the approval number of the pill, functions, usage, dosage, storage conditions, expiration dates for use, and the manufacturer’s name. The drugs will be administered by an independent clinical assistant in each center, who will take responsibility for the drug’s distribution, storage, and return. All drugs will be registered in the “drug-use record for clinical trials,” including information on the date of release of the trial drugs, the names of the subjects, and the quantities of drugs provided and retrieved. According to the intervention plan, there will be 6 medium packages contained in each large package and 112 small bags of drugs (12.1 g/bag) (Table 2) in each medium package. The patients will be randomly divided into the Elian Granules treatment group and the placebo control group. All drugs will be taken with hot water half an hour after meals, two small bags each time, twice a day for 24 weeks. Follow-up visits will be arranged at 4, 12, and 24 weeks after treatment. After the clinical study, the patients will receive routine treatment.

**Table 2 Tab2:** Components and dose of Elian Granules

Formula name	Chinese name	English name	Weight (g)	Weight (%)
Elian Granules	Ezhu	Zedoary turmeric	0.275	2.27
	Huanglian	Coptis	0.125	1.03
	Dangshen	Codonopsis	2.25	18.59
	Danshen	Salvia	0.8	6.61
	Danggui	Angelica	1.625	13.43
	Pugongying	Dandelion	1.475	12.19
	Baihuasheshecao	Oldenlandia diffusa	1.075	8.88
	Baizhu	Rhizoma atractylodis	1.65	13.64
	Shenggancao	Raw licorice	0.275	2.27
	Banxia	Pinellia	1	8.26
	Chenpi	Tangerine peel	0.55	4.55
	Fuling	Tuckahoe	1	8.26
	Total		12.1	100

### Criteria for discontinuing or modifying allocated interventions {11b}

Patients will be able to leave the study at any time for any reason if they wish to do so without any consequences. The patient’s participation in this study can also be ended by the investigator if the patient is uncooperative and/or does not attend study visits. The patient data that have been collected up to that point will be included in the analysis. This study will be prematurely ended in the event of multiple adverse events. The criteria for study termination include any suspected unexpected serious adverse reaction (SUSAR) or serious adverse event (SAE) based on an allergic reaction and clear allergic or iatrogenic effects in two or more patients.

### Strategies to improve adherence to interventions {11c}

During the clinical trial, to ensure the compliance of the subjects, it is important that they fully understand the significance of the trial, the importance of taking the medicine on time, and the necessity for follow-up. The subjects will be required to take the medicine according to the regulations and to fill in the patient diary card on time. The drug counting method (medication compliance = (actual dosage/required dosage) × 100%) combined with inquiry will be used to judge the compliance of the subjects taking the test drug. These issues will be fully and patiently explained to the participants, who will be asked to take the medicine and attend the follow-up as required.

### Relevant concomitant care permitted or prohibited during the trial {11d}

In addition to prescribed medication, the following traditional Chinese and Western medicines, as well as other factors that could potentially affect chronic atrophic gastritis, will be prohibited during the trial period. If a participant is found to be taking these drugs, they will be withdrawn from the study.The use of other drugs, such as folic acid, selenium, yeast, vitamin C, and vitamin E, will not be allowed [7]The use of Chinese patent medicines that may have curative effects, including the reversal or slowing of atrophy progression, will also not be allowed. These medicines include Weifuchun, Jinghuaweikang capsules, moluodan, Dalitong granules, Qizhiweitong granules, bilingweitong granules, Wenweishu capsules, Xiaojianzhong capsules, Yangweishu capsules, Zhizhukuanzhong capsules, and Weisu granules, among others, as well as any Chinese herbal decoctionNo any acupuncture therapy for treating chronic atrophic gastritis will be allowed during the trial

It will also not be allowed to use any drugs which have a therapeutic effect on gastritis, such as PPIs and/or prokinetic agents during the study.

Drugs or other treatments that are required to be taken continuously for the treatment of complex diseases can be used under the guidance of researchers. Any drugs used during the trial must be recorded and explained in detail in the study cases, including the name of the disease, drugs, dosage, and usage, so that they can be analyzed and reported when summarized.

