### Outcomes {12}

#### Primary outcome

The histological assessment of gastric mucosal biopsies is the primary outcome of the study. OLGA and OLGIM staging will be used for pathological evaluation. The evaluation will be performed both before and after 24 weeks of administration of the treatment and any histopathological changes in the gastric mucosa will be compared between the two groups before and after 24 weeks of treatment. The outcomes will be divided into progressive, stable, and improved according to the OLGA/OLGIM stage after treatment. An increase in staging grade will represent progression, an unchanged staging grade will represent stability, and a reduction in staging grade will be considered an improvement.

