## Statistical methods

### Statistical methods for primary and secondary outcomes {20a}

Full analysis set (FAS): this refers to the ideal subject set that is as close as possible to the principle of intention to analyze (including all subjects who are randomized into the group and receive at least one treatment). For the estimation of missing values of major variables, if the case data of all treatment processes cannot be observed, they will be carried forward to the missing data of the test, ensuring that the number of subjects evaluated for efficacy at the end is consistent with that at the beginning of the trial.

Per protocol set (PPS): the main variables are able to be determined for all patients who meet the experimental treatment protocol, have good compliance, use 80–120% of the experimental drugs, and complete the CRF requirements, with no missing baseline variables and no major violation of the experimental protocol.

Safety analysis set (SS): all subjects who received at least one treatment after randomization.

The main variables and comprehensive efficacy analysis constitute the full analysis set and the per-protocol set; demographic and other baseline characteristics will be analyzed using the full analysis set; the safety set will be selected for safety evaluation.

Baseline equilibrium analysis will be conducted in FAS.

The equilibrium analysis of the basic value is aimed at the basic demographic characteristics, vital signs, and curative effect-related indicators, among others, on enrollment into the group, to explain whether the basic characteristics of the two groups are comparable. Among them, the quantitative indicators (such as age, course of disease, temperature, pulse, respiration, systolic blood pressure, diastolic blood pressure, and TCM syndrome score) of the two groups will be listed, including the number of cases, means, standard deviations, medians, maxima, and minima. The two groups will be compared by ANOVA and the Kruskal-Wallis rank sum test. The frequencies and percentages of qualitative indicators (such as nationality, marital status, heart rate, history, allergy history, single symptom) will be listed and compared by *χ*^2^ test/precise probability method/rank sum test.

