### Adverse event reporting and harms {22}

The safety of subjects during the study period is very important, and every adverse event will be recorded in detail on the adverse event form (AEF). Adverse events (AE) include any new disease, aggravation of the original disease, and complications related or unrelated to treatment. Any fatal, life-threatening, disabling, or serious event that results in hospitalization or long-term hospitalization will be considered to be an SAE. All these data will be recorded on the AEF along with the corresponding treatment methods and will be reported to the China Food and Drug Administration (CFDA), the Provincial Food and Drug Administration, and the ethics committee within 24 h. Adverse events will be reported to the other research centers at the same time. The severity of acute events will be divided into three grades: mild, moderate, and severe. A mild event represents a small amount of physical discomfort, with no intervention necessary, and having no effect on the study. Subjects experiencing severe events will, for their own safety, be withdrawn from the study. In the case of SAE, the researchers will be able to confirm the treatment allocation of the subjects through emergency unblinding. Any AE related to the trial drug will be treated free of charge. In addition, all adverse events will be recorded and tracked until they have been properly resolved or have stabilized. Any abnormal physical or chemical indices recorded after the medication will be reexamined to ensure that they return to normal or become stable.

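### Two protocol rules withdraw patients from the study before the only post-baseline biopsy, so their primary outcome becomes stable by construction, which conflicts with the stated intention analysis

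*Protocol article*

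**What the plan says.** **Withdrawal.** Section {11d} lists prohibited supplements, Chinese patent medicines, herbal decoctions and acupuncture, and states: "If a participant is found to be taking these drugs, they will be withdrawn from the study". A separate paragraph after the list also bars drugs that act on gastritis, "such as PPIs and/or prokinetic agents during the study". Section {22} adds: "Subjects experiencing severe events will, for their own safety, be withdrawn from the study". Section {6b} lets the investigator withdraw a patient whose condition changes and who needs other treatment.

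**Data kept.** Section {11b}, on patients who leave by choice or whose participation the investigator ends for poor cooperation or missed visits, says: "The patient data that have been collected up to that point will be included in the analysis".

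**Primary outcome.** "The evaluation will be performed both before and after 24 weeks of administration of the treatment". Table 5 shows biopsy at Visit 1 and Visit 5 (week 24) only, and no early-termination visit. In the primary outcome definition, "an unchanged staging grade will represent stability".

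**Analysis.** Section {20a} describes the FAS as "as close as possible to the principle of intention to analyze". Every randomized patient who was treated at least once belongs to it. Missing values of major variables are carried forward so that the number assessed at the end matches the number at the start. Section {20c} says that the study will be evaluated by intention analysis and credits this with keeping missing data to a minimum.

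**The concern.** The protocol does not distinguish stopping study treatment from leaving the study. A patient caught by either rule has no week-24 biopsy, and the fill-in then supplies a result that nobody observed. An intention-to-treat evaluation needs the outcome after such events, so calling the analysis an intention analysis cannot reduce missing data that the conduct rules create.

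What is at stake is the primary comparison. Severe events may depend on treatment. Use of symptomatic gastritis drugs may depend on how the patient is doing. If such losses differ between arms, the two arms receive different shares of patients scored stable by rule, and that alone can create or hide a difference.

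**Working it through.** **1. The plan's own figure.** Section {14} gives 95 per group from 85% vs 63.3%, α = 0.05, power 0.90. Pooled two-sided formula: p̄ = 0.7415, so n = [1.96·√(2·0.7415·0.2585) + 1.2816·√(0.85·0.15 + 0.633·0.367)]² / 0.217² = 83.4, or 84 per arm. With continuity correction: (83.4/4)·[1 + √(1 + 4/(83.4·0.217))]² = 92.4, or 93. That is within 2 of 95. The planned total of 240 gives 120 per arm.

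**2. What happens to a withdrawn patient.**
- Sections {11d} and {22}: the patient leaves the study.
- Table 5: no biopsy falls between enrollment and week 24, so the only histology value is the baseline one.
- FAS rule in {20a}: earlier values are carried forward.
- Primary outcome definition: an unchanged stage is classed as stable.

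The result is therefore fixed by rule. Section {22} follows adverse events to resolution or stabilization. Section {18b} speaks of contacting patients to complete follow-up, but does not mention withdrawn patients or biopsies. No section provides for a week-24 biopsy after withdrawal.

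**3. Illustration of size.** Loss rates are assumptions; the documents give none. Let p be the true success rate in both arms (no true effect), and a and b the loss proportions in the arms with less and more loss.
- Success = improved only (lost patients fail): observed rates are p(1−a) and p(1−b), and the false difference is p(b−a).
- Success = improved or stable (lost patients succeed): the false difference is −(1−p)(b−a).

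Rejection probability comes from a two-sided 5% pooled two-proportion test with 120 per arm (normal approximation), in place of the planned center-stratified CMH test. Example with p = 0.50 and 15% vs 25%: rates 0.425 and 0.375, d = 0.050, SE under the null 0.06325, SE under the alternative 0.06316. Rejection = Φ[(0.050 − 0.1240)/0.06316] + Φ[(−0.050 − 0.1240)/0.06316] = 0.121 + 0.003 = 0.124.

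| Assumed loss | p | Improved only: difference, rejection | Stable also success: difference, rejection |
|---|---|---|---|
| 2% vs 5% | 0.30 | +0.9 points, 5.3% | −2.1 points, 6.4% |
| 2% vs 5% | 0.50 | +1.5, 5.6% | −1.5, 5.6% |
| 2% vs 5% | 0.633 | +1.9, 6.0% | −1.1, 5.4% |
| 15% vs 25% | 0.30 | +3.0, 8.4% | −7.0, 19% |
| 15% vs 25% | 0.50 | +5.0, 12.4% | −5.0, 12.4% |
| 15% vs 25% | 0.633 | +6.3, 16.5% | −3.7, about 10% |
| 20% vs 20% | any of these | 0, 5.0% | 0, 5.0% |

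A plus sign favours the arm with less loss.

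**4. Power under equal loss.** If 20% are lost in each arm and the planning rates are read as improvement rates, 0.85 vs 0.633 becomes 0.680 vs 0.506, and power at 120 per arm falls from 0.974 to 0.785. If stable also counts as success, the rates are 0.880 vs 0.706 and power is 0.918. These figures are for loss of every kind, not only for the two rules.

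**The case against.** Several stronger readings are tempting, and the documents do not carry them.

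- **That the losses are outcome-related.** This is an inference. The section on clinical manifestations says that dyspepsia and its severity do not correlate significantly with histopathological stage, so symptom-driven drug use is not shown to track the primary outcome. Possibly treatment- or outcome-related is as far as the text goes. The mechanism needs only loss that differs by arm.
- **That PPI or prokinetic use expressly ends participation.** The withdrawal sentence introduces the list. The PPI and prokinetic ban comes after it and has no withdrawal sentence of its own. The reading is plausible, not explicit.
- **That section {11b} discards later data from these patients.** Its sentence on data follows other reasons for leaving. It fits the same pattern but was not written about prohibited drugs or severe events.
- **That the FAS drops these patients or makes no attempt at intention to treat.** It keeps every randomized patient who received treatment. The defect is that their outcome is not observed. For the same reason, heavy loss reduces the number of completers, not the FAS count.
- **That the false-positive rate is 8–16%.** This needs a 10-point imbalance that the documents do not suggest, and one definition of success. Some of any such loss would be voluntary and would remain after the fix. Part of the effect also belongs to the carry-forward rule, which could be criticized separately.

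What stands is the chain in step 2 of the working. It uses stated rules only, and no later analysis plan can recover a biopsy that was never taken.

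**Conclusion.** The point holds as an internal conflict with a possible bias of unknown size. The conduct rules remove patients before the only post-baseline measurement of the primary outcome, the FAS then scores them as stable, and section {20c} claims an intention analysis that limits missing data.

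The effect on type I error ranges from negligible (about 5–6% at 2% vs 5% loss) to material (8–16% at 15% vs 25%) when missing is scored as not improved. It is nil when loss is equal between arms. The direction cannot be stated, because the protocol does not say whether stable counts as success. All of this rests on assumed loss rates, no true effect, 120 per arm and baseline carried forward. The change is worth making because it is cheap, not because a large bias has been shown.

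**What to change.** Leave the prohibited-drug and severe-event treatment rules unchanged. Amend only the follow-up:

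- Separate stopping study treatment from leaving the study in {11b}, {11d} and {22}, and state whether the paragraph on PPIs and prokinetics falls under the withdrawal sentence.
- Unless consent is withdrawn or endoscopy is judged unsafe, keep these patients in the study for the week-24 endoscopy, biopsy, symptom score and SF-12.
- Use those data in the FAS. Exclude such patients from the PPS under its existing major-violation rule, and say so for both groups.
- Bring the statement in {20c} into line with what is then done.

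**Cost:** a short amendment and an eCRF flag. The week-24 assessments are already in Table 5 for every patient, so no new procedure is added. The downside is some effort to bring back patients who are off treatment. The trial status section reports 81 patients already included, and any of them already withdrawn may not be recoverable.
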